**Trial sample size and power**

The mean difference in DAOH was assumed to be 20 days (586 Vs 566 days with a standard deviation of 69 days) at two-year. We used the DAOH at two-year from the Trivandrum Heart Failure Registry in the sample size calculation
^
7
^. In the intervention group, we assumed 3% higher DAOH. A sample size of 770 HF participants per group (a total of 1540), in 11 equal clusters per arm (total 22 clusters) provides 91% power for a 2-sided 5% alpha. Assumptions; an ICC of 0.01 (design effect 2.08), coefficient of variation of cluster size of 0.85.

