## Introduction

Globally, heart failure (HF) is a major public health problem with relatively high morbidity and mortality. The number of individuals with HF is estimated to be in the range of 1.3 to 4.6 million in India
^
1–
3
^. Additionally, the number of deaths due to HF in India showed an increase of 138 percent from 1990–2013
^
2
^. Based on the best available estimates, the incidence of HF in India is 1 per 1000 population
^
2
^. In consistent with findings from many high-income countries, the predominant etiology of HF is ischemic heart disease (IHD) in India
^
4
^. Due to the steady increase in the absolute number of individuals with IHD over the last three decades
^
5,
6
^, HF burden is expected to grow substantially in India.

Heart failure patients in India receive sub-optimal treatment and experience high mortality. For example, only one of four eligible HF patients receives guideline-directed medical therapy (GDMT) at discharge
^
2,
7
^. Similarly, one of three patients adhered to GDMT in a large study in India involving 15,870 patients with reduced left ventricular ejection fraction (EF<40%)
^
8
^. Additionally, one of five patients died within three months of follow-up
^
2
^. The long-term prognosis of HF is also poor with a median survival time of 3.7 years
^
9
^. However, those who received GDMT experienced lower mortality and survived longer
^
2
^. Data from the Kerala Heart Failure Registry
^
10
^, and the National Heart Failure Registry
^
4
^ also demonstrated survival benefits in patients who received GDMT during index hospitalisation. Further, the survival benefits of GDMT persisted up to five years of follow-up
^
9
^.

Physician driven quality improvement initiatives in HF management may not be feasible, scalable, and effective in India. The PINNACLE India quality improvement programme concluded that in a country with a disproportionate provider/patient ratio and low levels of government funding for quality improvement, physician-driven initiatives for practice-based learning and improvement are extremely difficult
^
11
^. The key barriers include lack of electronic medical records, virtually non-existent outpatient record-keeping, and difficulty of engaging physicians due to their busy clinical schedules
^
11
^. To overcome these barriers, we propose a task sharing strategy of empowering trained nurses as facilitators of HF care in India.

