**Data analysis plan**

Aim1: All interviews conducted in local language (Malayalam) will be simultaneously translated to English and transcribed. Interviews conducted in English language will be transcribed. The data analysis will follow a framework method of analysis
^
55
^. After the data is transcribed, the transcripts will be read line-by-line to get familiarised with the data. First a few transcripts will be coded using an inductive method. Later, a working analytical framework will be generated by merging the initial codes. The working analytical framework will then be used to index the remaining interviews. After indexing all the interviews, key themes will be generated by merging categories having similar meaning for each stakeholder. Finally, the data will be interpreted based on the convergences and divergences between the data themes across different stakeholders.

 Aim 2: All quantitative analysis will follow guidelines of cluster randomised trials
^
56
^. We will employ intention to treat analysis except in the sub-group analyses. Initially, baseline characteristics will be compared by treatment group to examine the adequacy of randomisation. The primary analysis will be a complete case analysis. However, missing data on outcome variables will be reported and sensitivity analyses will be conducted after multiple imputation of missing data.

The DAOH will be calculated by subtracting days in hospital and days from death until end of study follow-up from the total follow-up time of 730 days. The DAOH is a patient-centred outcome, which accounts for multiple events over the two-year course of a study period, weighs death more than hospitalisation, and deaths occurring early more than those occurring later. Empirical density curves will be created to show the distribution of DAOH over two-year follow-up period, stratified by intervention group. The median and the interquartile range of DAOH by treatment group will be provided. Poisson regression with a robust variance estimate
^
57
^ and an offset term to account for clustering will be employed in the analyses of DAOH per two-years of follow-up time. This procedure will yield a rate ratio and 95% CI
^
57
^. The rate ratio is the DAOH in the intervention arm divided by DAOH in the enhanced usual care arm. A rate ratio of >1 indicates more DAOH in the intervention arm in comparison to the usual care arm (i.e., favours the intervention).

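### The planning SD of 69 days for two-year DAOH does not fit the early mortality the protocol cites, so the stated 91% power is not supported and is probably much lower

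*Protocol article*

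**What the plan says.** All references are to the protocol article.

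- **Trial sample size and power**, planning values: "The mean difference in DAOH was assumed to be 20 days (586 Vs 566 days with a standard deviation of 69 days) at two-year". The DAOH is attributed to a heart failure registry (reference 7). The next assumption is "In the intervention group, we assumed 3% higher DAOH".
- **Same section**, size and clustering: "A sample size of 770 HF participants per group (a total of 1540), in 11 equal clusters per arm (total 22 clusters"), with "an ICC of 0.01 (design effect 2.08), coefficient of variation of cluster size of 0.85". This "provides 91% power for a 2-sided 5% alpha".
- **Data analysis plan, Aim 2**, outcome, on a scale of 730 days: "The DAOH will be calculated by subtracting days in hospital and days from death until end of study follow-up from the total follow-up time of". Time after death therefore scores zero.
- **Introduction**, prognosis of heart failure patients in India: "Additionally, one of five patients died within three months of follow-up" (reference 2), and "The long-term prognosis of HF is also poor with a median survival time of 3.7 years" (reference 9).

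The article shows no derivation of the 69 days and does not set it against the mortality figures.

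**The concern.** DAOH in a population with appreciable mortality has a long lower tail: early deaths score near zero, while survivors with few admissions score near 730. That gives a large between-patient SD. An SD of 69 around a mean of 566 leaves almost no room for early deaths, yet the protocol uses high early mortality to justify the trial.

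The SD drives the power calculation. If it is too small by a factor of two or three, the trial has little chance of detecting 17 to 20 days. A null result read under a claimed 91% power would then be taken as evidence that collaborative care does not work, when the data could not have shown it either way.

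**Working it through.** **Inputs.** From the sample size section: means 586 and 566, SD 69, 3% effect, 770 per arm, design effect 2.08, two-sided 5%. From the Data analysis plan: a 730-day scale. From the Introduction: 20% dead by about day 90, median survival 3.7 years.

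**1. Reproduce the stated power.** SE = SD × √(2 × 2.08 / 770) = SD × 0.0735, and power = Φ(difference/SE − 1.96). At SD 69, SE = 5.07 days.
- 3% effect: 0.03 × 566 = 16.98 days. Φ(16.98/5.07 − 1.96) = 91.7%, which matches the stated 91%.
- 20 days: Φ(20/5.07 − 1.96) = 97.6%, which does not match.

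The 91% therefore belongs to the 3% effect. The quoted 20 days is 20/566 = 3.5%.

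**2. How many early deaths does SD 69 allow?** By the one-sided Chebyshev (Cantelli) inequality, with 566 − 90 = 476, the share at or below 90 days is at most 69² / (69² + 476²) = 4,761 / 231,337 = 2.1%. No distributional shape is assumed. The cited figure of 20% is about ten times that.

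**3. Smallest SD for a given early mortality.** With mean 566 and a share p at or below 90 days, SD ≥ 476 × √(p/(1 − p)):
- p = 5%: 109 days
- p = 10%: 159 days
- p = 20%: 238 days

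These are floors. They place all early deaths at day 90 and give everyone else one identical score.

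**4. Cross-check on long-term survival.** Assume exponential survival with median 3.7 years and ignore hospital days. Then λ = ln 2 / (3.7 × 365.25), survival at two years is 69%, mean DAOH is 609 and SD is 215.

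**5. Power at these SDs** (design effect kept at 2.08):

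| SD (days) | Basis | Power, 20 days | Power, 17 days |
|---|---|---|---|
| 69 | as planned | 97.6% | 91.8% |
| 109 | floor, 5% dead by day 90 | 70% | 56% |
| 159 | floor, 10% | 40% | 31% |
| 215 | exponential, 3.7-year median | 24% | 19% |
| 238 | floor, 20% | 21% | 16% |

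Two constructed scenarios, both with 69% alive at two years, give these powers for 20 days:
- No deaths before day 90: SD 181, power about 32%.
- 20% dying evenly over the first 90 days: SD 282, power about 16%.

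Power of 80% needs an SD of at most 97 days for a 20-day difference, or 83 days for 17.

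**6. Precision at SD 215 to 238.** SE is 15.8 to 17.5 days. The difference detectable with 90% power is (1.96 + 1.28) × SE, about 51 to 57 days. The 95% CI half-width is 1.96 × SE, about 31 to 34 days.

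**The case against.** **Different sources.** The planning DAOH cites reference 7, while the mortality figures cite references 2 and 9. Nothing shown says these are the same cohort, or that the 20% refers to patients with reduced ejection fraction. This stands. An SD of 69 with mean 566 is possible in principle on a 0 to 730 scale. It is excluded only in combination with a mortality assumption, so a reader who infers that the planning values are impossible in themselves goes too far. Relaxing the assumption does not rescue the figure, because 5% dead by day 90, a quarter of the cited rate, already requires an SD of 109. If deaths were rare enough for SD 69, the average loss of 730 − 566 = 164 days would have to come largely from hospital stays, and nothing in the article suggests that.

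**The scenarios disagree.** The exponential with a 3.7-year median has mean 609, not 566, and implies only about 4.5% dead at 90 days. The 238-day floor is a two-point distribution. This also stands: they show a range and do not estimate one SD.

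**The analysis is a Poisson rate ratio.** Its robust variance depends on the same between-patient spread, and the protocol itself powers the trial on a mean difference.

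**The trial's own confidence interval will show the real precision.** True, but the published 91% will still colour how a null result is read.

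**Conclusion.** The SD of 69 days is not compatible with mean DAOH of 566 and early mortality anywhere near what the protocol cites, so the 91% power is unsupported. Across the scenarios examined, power for 20 days runs from about 16% to 70%. For the 17-day effect behind the stated 91%, the tabulated SDs from 109 to 238 give about 56% down to 16%.

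This assumes that early mortality in the planning population is at least 5% (for the mildest figure) up to the cited 20%, and that the stated ICC and design effect hold at the larger SD.

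Two stronger readings are tempting but not supported:
- **Power is 20 to 25%.** That mixes scenarios with different means and medians, and sets 20-day power against a 91% that belongs to 17 days. Like for like, at SD 215 to 238, the comparison is 97.6% against 21 to 24% for 20 days, or about 91% against 16 to 19% for 17 days.
- **The 69 is really a standard error, or an SD among survivors.** With an SD of 215 to 238, a standard error of 69 implies only (215/69)² to (238/69)², about 10 to 12 patients. Among two-year survivors, a mean of 566 would require 164 hospital days each. The origin of the 69 is not shown.

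**What to change.** 1. Re-derive the patient-level SD of two-year DAOH from the registry data with deaths counted as the Data analysis plan defines, and state the registry's 90-day and two-year mortality beside it.
2. Choose one effect size, 17 or 20 days, and use it throughout the sample size section.
3. Restate the power and the minimum detectable difference. If the SD is 215 to 238, the latter is about 51 to 57 days at 90% power.
4. Confirm the SD and ICC later from blinded trial data with arms pooled, once enough patients have completed two years.
5. State before unblinding that a non-significant result will be interpreted from its confidence interval, and not as evidence of no effect under 91% power.

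**Cost.** A registry calculation and an amendment to the protocol or analysis plan, with no extra patients and no change to the outcome or analysis. The registry step can be done promptly. The blinded check comes only late, because each patient needs two years of follow-up. The downside is a less favourable stated power.

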Caregivers of patients with HF	In-depth interview Total 10–12 IDIs	● Perceptions and behaviours on clinical management, lifestyle, and self-care ● Feedback on proposed intervention components and methods ● Gauge caregivers’ interest and acceptability
Physicians Nurses Dieticians Physiotherapists	In-depth interview 10–12 interviews in each category (30–36 total interviews)	● Perceived quality of HF care ● Perceived patient barriers and facilitators to delivery of care, lifestyle change, and self-care ● Gauge feasibility of planned intervention components

**
*Collaborative care model intervention (Aim 2)*
**

A parallel group cluster RCT of more than 1500 adult HF patients with reduced ejection fraction from 22 units in India
^
36
^ will be used to address Aim 2. Each participating unit will be randomly assigned to one of two arms: 1) those delivering a comprehensive CCM (intervention) or 2) those delivering standard of care (usual care).

The selected hospitals will be independent units with dedicated staff employed at each site for recruitment and follow-up of patients included in the trial. The site teams will have similar compositions in terms of clinical roles.

Cluster eligibility criteria: Eligible units will include HF centres of major hospitals from the national heart failure registry or Kerala heart failure registry that serve ≥80 new patients in six-months and consented to the randomisation plan. All HF patients will also be required to provide individual consent to participate in the study.

Patient eligibility criteria and randomisation: Potential participants must meet the standard definition of HF
^
37
^ (HF with reduced ejection fraction of <40%) based on echocardiography to be eligible to enter the study. Consecutive patients will be recruited from the participating centres. Eligible units will be randomised at one time point, prior to trial implementation. The allocation ratio will be 1:1. Randomisation procedures will not be blocked, restricted, or matched. We will use computer generated random numbers to allocate half of the units to each arm of the study.

*Duration of treatment period and follow-up*

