**Study coordination**

Sree Chitra Tirunal Institute of Medical Sciences and Technology (SCTIMST), Trivandrum, India will be the study coordinating centre and trial sponsor. There will be 22 participating centres in India including SCTIMST. Hospitals with facilities for management of HF will serve as the cluster units or participating centres. Each participating centre will be recruiting 70 patients.

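### The power paragraph is internally inconsistent: its own inputs give about 97% power for 20 days rather than 91%, 20 days is not 3% of 566, and 2.08 is not reproduced by the stated ICC, CV and 70 patients per centre

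*Protocol article*

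**What the plan says.** All but one of the relevant figures stand in one paragraph of the protocol article, under *Trial sample size and power*.

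- Effect in days: "The mean difference in DAOH was assumed to be 20 days (586 Vs 566 days with a standard deviation of 69 days) at two-year".
- Effect as a percentage: "In the intervention group, we assumed 3% higher DAOH".
- Size: "A sample size of 770 HF participants per group (a total of 1540").
- Clusters and power: "in 11 equal clusters per arm (total 22 clusters) provides 91% power for a 2-sided 5% alpha".
- Clustering assumptions: "an ICC of 0.01 (design effect 2.08), coefficient of variation of cluster size of 0.85".

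Under *Study coordination* the article adds: "Each participating centre will be recruiting 70 patients". This agrees with 770/11 = 70 and 22 × 70 = 1540.

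**The concern.** Three things in this paragraph do not agree.

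1. The effect is given twice, as 20 days and as 3%, and on a base of 566 these are different effects.
2. The power does not follow from the difference, SD, sample size and design effect printed beside it.
3. The clusters are called equal, with 70 patients planned at each centre, yet a large CV of cluster size is assumed. The printed design effect matches neither assumption.

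The target difference is the yardstick against which the primary result will be read, and the power statement tells readers what a null result would mean. If the two come from different calculations, neither can be relied on as printed.

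**Working it through.** **Inputs** (all from *Trial sample size and power*, except the 70 per centre, which is also in *Study coordination*): difference 20 days (586 − 566); SD 69; n = 770 per arm; 11 clusters per arm; m = 770/11 = 70; ICC 0.01; CV 0.85; design effect (DE) 2.08; two-sided alpha 5%.

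**Step 1. The effect.** 0.03 × 566 = 16.98, which gives 583. The printed mean of 586 is 586/566 = 1.035, or 3.5% higher.

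**Step 2. The plan's own power figure.** SE = SD × √(2 × DE / n) = 69 × √(2 × 2.08 / 770) = 5.07 days. By the normal formula, power = Φ(difference/SE − 1.96).

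- 20 days: 20/5.07 = 3.94, and Φ(1.98) = 97.6%.
- 17 days: 17/5.07 = 3.35, and Φ(1.39) = 91.8%.

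The stated 91% is therefore not reproduced for 20 days. Getting 91% at 20 days would take a design effect of about 2.97, or an SD of about 82 days at DE 2.08 (about 80 at DE 2.20).

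**Step 3. The design effect.** The usual formula for unequal clusters is DE = 1 + [(1 + CV²) × m − 1] × ICC.

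- CV 0.85: 1 + [(1.7225 × 70) − 1] × 0.01 = 2.196, or 2.20.
- Equal clusters (CV 0): 1 + 69 × 0.01 = 1.69.
- Finite-cluster version, with CV² multiplied by (k − 1)/k: 2.15 for k = 11 and 2.17 for k = 22.
- Relative-efficiency formula: 2.05.

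None of these equals 2.08. With the usual formula at m = 70, 2.08 corresponds to a CV of about 0.75.

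**Step 4. Power across the design effects** (770 per arm, SD 69; t uses the noncentral t on 22 − 2 = 20 df):

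| Design effect | 20 days, normal | 20 days, t | 17 days, normal | 17 days, t |
|---|---|---|---|---|
| 1.69 (equal clusters) | 99.2% | 98.6% | 96.1% | 94.2% |
| 2.05 (relative efficiency) | 97.8% | 96.5% | 92.2% | 89.5% |
| 2.08 (as stated) | 97.6% | 96.3% | 91.8% | 89.0% |
| 2.15 (finite-cluster, k = 11) | 97.2% | 95.8% | 90.9% | 88.0% |
| 2.20 (usual formula) | 97.0% | 95.4% | 90.4% | 87.3% |

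Every 20-day entry is at least four points above 91%. The 17-day entries for unequal clusters lie between 90% and 92% by the normal formula and between 87% and 90% with t.

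**The case against.** **The target is clear, because 20, 586 and 566 are all printed and agree.** This is fair as far as it goes, and 3% can be read more loosely. Over the 730-day follow-up given in the *Data analysis plan*, 20/730 = 2.7 percentage points; relative to 586, 20 days is 3.4%. Either rounds to 3. But the sentence speaks of the intervention group being higher, which most naturally means relative to the control mean of 566. And if 20 days is accepted as the target, the mismatch with 91% remains in full.

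**A reader might infer that the 91% was calculated for 17 days.** The near match makes this plausible, but the article mentions neither 17 days nor 583. The match is also inexact: at the stated design effect, 17 days gives 91.8% by the normal formula and 89.0% with t. It remains a possible explanation only.

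**A reader might also infer that 2.08 is simply impossible for a CV of 0.85.** That goes too far. The formulas above run from 2.05 to 2.20, so 2.08 lies within their range. The usual formula gives 2.075 with 63 patients per centre, which is 70 less 10%. That loss rate is an assumption that the article does not state, and it does not rescue the paragraph: with 693 per arm and DE 2.08, power is 96.3% for 20 days and 88.9% for 17 days (normal formula).

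**Assuming unequal clusters while planning equal ones is conservative.** This is true of power. It does not remove the contradiction in the text. Even if the word equal was meant only for the number of clusters per arm, a fixed 70 per centre still does not sit with a CV of 0.85.

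**No loss rate is given.** A condensed article may leave this to the full protocol, so its absence is not part of this point. Whether to use a t reference is likewise a choice of method; the point is only that the choice should be named.

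**Conclusion.** The point holds as an inconsistency in the printed figures. On the stated 20 days, SD 69, 770 per arm and design effect 2.08, power is 97.6% (96.3% with t on 20 df), so 91% understates it by about five to seven points. The two statements of effect differ by 3 days (17 against 20). At 70 per centre the design effect is 2.20 by the usual formula for CV 0.85, or 1.69 for equal clusters.

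The conclusion takes the SD of 69 and the ICC of 0.01 as given and compares two means with a design-effect adjustment.

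A reader might infer that the trial is underpowered. These figures do not show that. For 20 days there is power to spare, and for 17 days it is about 90% by the normal formula even with a design effect of 2.20 (87% with t on 20 df). What is at fault is the reporting of the power and of the target difference.

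**What to change.** Rewrite the one paragraph so that each figure follows from the others:

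- State a single target difference: 20 days (3.5%) or 17 days (3%).
- State a single cluster-size assumption: either delete the word equal, keep the CV of 0.85 and reconcile it with the 70 planned per centre; or keep equal clusters and drop the CV.
- Recompute the design effect from that assumption (2.20 or 1.69 by the usual formula). If another formula was used, name it.
- Restate the resulting power and name the reference distribution. With a design effect of 2.20 and the normal formula this is about 97% for 20 days or 90% for 17 days; with 1.69 it is about 99% or 96%.

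The cost is one corrected paragraph and a changed power figure. Sample size, number of centres and trial conduct stay as they are.

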**Study coordination**

Sree Chitra Tirunal Institute of Medical Sciences and Technology (SCTIMST), Trivandrum, India will be the study coordinating centre and trial sponsor. There will be 22 participating centres in India including SCTIMST. Hospitals with facilities for management of HF will serve as the cluster units or participating centres. Each participating centre will be recruiting 70 patients.

**Data entry and data management**

Qualitative data will be collected by trained post-doctoral fellows and research fellows using in-depth interview guide for each stakeholder. All the interviews will be audio-recorded with permission of the participants.

Quantitative data will be collected by trained nurses or research co-ordinators using study questionnaire. Training will be provided for collection of clinical data and personal data from the patients. Nurses/research co-ordinators under the supervision of a principal investigator and the study post-doctoral fellows will do data entry on REDCap application using a tablet computer. The data will be cleaned, queries enquired and analysed by study post-doctoral fellows and research fellows. The study will collect both quantitative and qualitative data. The data will be de-identified to ensure confidentiality of the data.

